### Data management and statistical analysis

Anonymised data will be entered into a study database. The integrity of this data will be assessed by taking a random sample (10%) from the study database (after the completion of data collection) and comparing with the paper case report form (CRF). If there is less than 98% agreement between the paper CRF record and inputted measures, all data will be checked and rectified. The rectified database will be saved under a new filename (eg, studydatabase_rectified_date) and all changes made to the database will be logged. Essential trial documentation will be kept with the Trial Master File and Investigator Site Files. The sponsor will ensure that study documentation is retained in accordance with their local approvals after the conclusion of the trial.

As this is a proof-of-concept study, there is no formal plan for statistical analysis due to the small sample size and lack of statistical power. However, for a future trial an analysis plan has been developed which will be run in this study to determine its appropriateness. We will use intention to treat analysis with repeated measures general linear model analysis of variance for selected outcome measures and other appropriate tests for between-group and within-group analysis. We will also include correlations analysis and χ^2^ assumption testing.

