**Methods:**

A single (assessor) blinded pilot randomised controlled proof of concept study. 120 participants will be randomised to receive an 8-week home exercise programme consisting of either: (1) HOLOBalance or (2) The OTAGO Home Exercise Programme. Participants will be required to complete their exercise programme independently under the supervision of a physiotherapist. Participants will have weekly telephone contact with their physiotherapist, and will receive home visits at weeks 0, 3 and 6. Outcome measures of safety, acceptability and feasibility, clinical measures of balance function, disability, balance confidence and cognitive function will be assessed before and immediately after the 8 week intervention. Acceptability and feasibility will be explored using descriptive statistics, and trends for effectiveness will be explored using general linear model analysis of variance.

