Balance rehabilitation typically consists of personalised sets of exercises, defined by a healthcare professional and is the only effective treatment for balance disorders, irrespective of a person’s age.^32–34^ Although exercises are typically brief and easy to perform, there is up to 50% lost to follow-up rate in older adults in these programmes, and while supervision significantly increases compliance and effectiveness,^35^ it is costly to provide. To this end, many falls prevention programmes provide exercise programmes completed either in group settings or independently at home.^36–41^ These programmes have been shown to be effective in reducing falls rates in older adults, reducing falls by 30%–40% (dependant on target population), however, they are limited in that they either do not provide exercises to address vestibular function or dual task training,^37–39^ or these are not introduced until very late in the programme.^40 41^ This is despite promising evidence suggesting that combined cognitive and functional training may provide improvements beyond single task training.^42–44^ Similarly, rehabilitation programmes which address vestibular dysfunction (ie, multisensory rehabilitation, MSR programmes) have been developed for older adults at risk for falls and have shown substantial additional reduction of falls risk to standard programmes.^45–47^ These programmes require customised, expert-led interventions to optimise recovery, however, there is limited availability of experts to provide these individualised interventions and these may hinder their translation into clinical practice.

The HOLOBalance telerehabilitation platform has been developed to address this lack of expert physiotherapists. HOLOBalance will provide a customised and interactive falls rehabilitation programme that incorporates: (1) functional balance training, (2) multisensory exercises to improve balance function and (3) cognitive-motor training, for older adults at risk for falls. HOLOBalance will use off-the-shelf technologies to allow clinicians to provide an individualised balance rehabilitation programme for older adults who will be able to participate in at a time of their choice and in their home environment (for system description please visit www.holobalance.eu). This study protocol outlines the multisite randomised controlled proof-of-concept study to explore safety, feasibility and acceptability of the HOLOBalance telerehabilitation system.

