## Methods and analysis

### Trial design

This study is an assessor-blinded, randomised proof-of-concept study to explore the acceptability and feasibility of providing a home-based balance telerehabilitation programme (HOLOBalance) to community-dwelling older adults at risk for falls. All participants will be enrolled in a 8-week home exercise programme (HEP) designed to improve balance function, and which adheres to the current guidance for strength and balance training.^30^ All participants will receive an exercise programme provided under the supervision of a physiotherapist with regular reviews by telephone (weekly) and home visits (week 0, 3 and 6). Exercises will be prescribed according to participant feedback and task performance as assessed by the treating physiotherapist.

This study will compare acceptability of the HOLOBalance telehealth programme (eg, compliance, drop-out rate) to an established HEP that is routinely used in community rehabilitation (the OTAGO HEP^23^) and will explore trends for effectiveness across a number of validated outcome measures to explore whether a future trial is warranted, and if so to provide data for a sample size estimate. For this proof-of-concept study, data will be collected at baseline (week 0) and at completion of the intervention (week 9). The flow of participants through the trial will be recorded in compliance with the Consolidated Standards of Reporting Trials statement (figure 1), and this protocol has been developed using the Standard Protocol Items: Recommendations for Interventional Trials reporting guidelines for clinical trials.^48^

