### Randomisation

Patients will be randomised using an online platform (www.sealedenvelope.com) into either the intervention or control groups. Participants will be allocated in blocks of 10 with an allocation ratio of 1:1 to control (OTAGO HEP) and intervention (HOLOBalance) groups. Randomisation procedures will be run independently for each site and will be completed by a researcher external to the research study. No out of hours randomisation is required for this study.

Allocation will be concealed in consecutively numbered opaque envelopes which will be drawn up for each block and presented to the treating physiotherapist after the baseline assessment session has been completed. Allocation will not be revealed until after the baseline assessment has been completed, and once revealed will be entered onto the enrolment log.

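### With only two visits, the named repeated-measures ANOVA is a change-score comparison: less precise than adjusting for baseline, and it would oversize the future trial if its variance is used

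*Protocol article*

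**What the plan says.** The analysis method is named in Data management and statistical analysis: "We will use intention to treat analysis with repeated measures general linear model analysis of variance for selected outcome measures", followed by "other appropriate tests for between-group and within-group analysis". The Abstract (Methods) agrees: "trends for effectiveness will be explored using general linear model analysis of variance".

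The same section limits the status of this analysis: "there is no formal plan for statistical analysis due to the small sample size and lack of statistical power". It then gives the named method a purpose beyond this study: "for a future trial an analysis plan has been developed which will be run in this study to determine its appropriateness". The Abstract, Trial design and Sample size sections each say that the study should supply data for sizing a future trial.

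On timing, Trial design says "data will be collected at baseline (week 0) and at completion of the intervention (week 9"). Table 2 places the balance, cognitive and questionnaire scales at the baseline and follow-up test sessions only.

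On the design, the Randomisation section says "Randomisation procedures will be run independently for each site", so site is a stratum. The article lists no model factors or covariates, and it does not say how a missing week 9 value is handled.

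**The concern.** A repeated-measures ANOVA with one pre-treatment and one post-treatment value does use the baseline, but as a first outcome and not as a covariate. The group-by-time term then gives baseline a fixed weight of one, whatever its correlation with week 9. In a randomised comparison this costs precision for any correlation below 1.

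In a purely exploratory look at trends this would be a minor loss. It matters more here because the study is meant to judge whether this analysis suits a larger trial and to supply that trial's sample size inputs. An inefficient model could be carried forward, and a variance taken from it would make the next trial larger than it needs to be.

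A second, smaller matter is that the usual two-visit repeated-measures ANOVA analyses only participants with both values. The intention-to-treat label therefore needs a statement on missing week 9 data.

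**Working it through.** **Inputs from the article.** 60 participants per arm (Sample size), two visits (Trial design), three sites (Participants), 1:1 allocation run separately by site (Randomisation). The article gives no alpha, power, effect size, SD or correlation behind the 120, so there is no calculation to reproduce.

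**Assumed inputs.** Two-sided alpha 0.05; the same SD at both visits, set to 1; true difference 0.5 SD; correlation r between visits from 0.3 to 0.9.

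**Step 1: what the named test is.** With two visits, the group-by-time F test equals the square of the two-sample t test on change (week 9 minus baseline).

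**Step 2: variance per participant.**
- Change score: 2(1 − r).
- Week 9 adjusted for baseline: 1 − r².
- Ratio: 2(1 − r)/[(1 − r)(1 + r)] = 2/(1 + r).

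| r | change | adjusted | ratio | 60 per arm on change is worth, adjusted | power, change | power, adjusted |
|---|---|---|---|---|---|---|
| 0.3 | 1.40 | 0.91 | 1.54 | 39 per arm | 63.9% | 81.9% |
| 0.5 | 1.00 | 0.75 | 1.33 | 45 per arm | 78.2% | 88.5% |
| 0.6 | 0.80 | 0.64 | 1.25 | 48 per arm | 86.5% (86.47% unrounded) | 92.8% |
| 0.7 | 0.60 | 0.51 | 1.18 | 51 per arm | 94.2% | 97.0% |
| 0.9 | 0.20 | 0.19 | 1.05 | 57 per arm | 100% | 100% |

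**Step 3: the r = 0.6 row in full.**
- Change: SE = √(2 × 0.80/60) = 0.163; power = Φ(0.5/0.1633 − 1.96) = Φ(1.10) = 86%.
- Adjusted: SE = √(2 × 0.64/60) = 0.146; power = Φ(0.5/0.1461 − 1.96) = Φ(1.46) = 93%.

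**Step 4: check by simulation** (2000 runs per setting, 40 participants at each of three sites, no site differences). The spread of the estimates was 0.186 for change and 0.162 for ANCOVA at r = 0.5, and 0.140 and 0.130 at r = 0.7. Both methods were centred on the true 0.5.

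**Step 5: the future trial.** Required N is proportional to the variance. Sizing on the change-score variance instead of the baseline-adjusted variance multiplies N by 1.33, 1.25 or 1.18 at r = 0.5, 0.6 or 0.7.

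**Step 6: site.** A constant difference in level between sites cancels from the change score. At r = 0.5 the reported SE of the change comparison was 0.182 with or without site. Site matters only if the amount of change differs between sites. With assumed shifts of −0.3/0/+0.3 SD the reported SE was 0.188 without site and 0.182 with it; with −0.5/0/+0.5 SD it was 0.197 and 0.182. At r = 0.7 the larger shift gave 0.160 and 0.141. The change estimate and its actual spread were the same either way, so omitting site makes the reported SE conservative and adds no bias.

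**Step 7: missing week 9 values.** If a share d of participants has no week 9 value, an analysis needing both values keeps 60(1 − d) per arm. At an assumed d = 0.2 that is 48 per arm, and the SE rises by 1/√0.8 = 1.12. This applies to ANCOVA as well: with no visit between baseline and week 9, a participant with baseline only says little about the week 9 difference between arms.

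**The case against.** The strongest defence is that effectiveness is neither a primary outcome nor a powered comparison here. The article disclaims a formal analysis, speaks of trends, and runs the method precisely to see whether it is suitable. The fuller plan it mentions is not shown and may specify covariates, site and missing-data handling. Nor does the article say that a change-score SD will feed the future sample size, and the same data yield the raw SDs and the correlation, from which any design can be sized.

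Much of this stands. It limits the stakes and makes the inflation of the future N conditional. It does not remove the efficiency point, because the model class is stated in the article and trying it out for the next trial is its declared purpose.

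A reader might go further in several ways that the article does not support.
- **That the analysis is not intention to treat.** Leaving out site or a baseline covariate has no bearing on intention to treat. Missing-data handling does, but no complete-case rule is written; dropping participants is inferred from how the method is usually fitted.
- **That site is ignored.** No factors are listed at all, so site is unstated, not excluded.
- **That half the participants would be lost.** The Introduction's "there is up to 50% lost to follow-up rate in older adults in these programmes" is background on balance programmes generally, not a planning figure for this 8-week study, and the recommended model would not recover such losses.
- **That effectiveness will be judged on the group main effect**, which averages over both visits and dilutes the difference. The article names no such contrast; group by time is the usual one.

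**Conclusion.** The point holds as one of efficiency and planning. With two visits, the named analysis is a change-score comparison with 18% to 33% more variance than a baseline-adjusted one for r between 0.7 and 0.5. At r = 0.6 and a 0.5 SD effect, power is 86% against 93%. The same factor applies to the future trial's N if it is sized on change-score variance.

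The figures rest on an assumed r, an assumed effect and equal SDs at the two visits. The direction does not depend on equal SDs: with SDs s₀ at baseline and s₁ at week 9, the variance of change exceeds the adjusted variance by (s₀ − r·s₁)², which is never negative. The gain shrinks as r rises, to 5% at r = 0.9.

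Naming site in the model is sound because randomisation is run by site, but the expected gain is small unless sites differ clearly in change. Missing week 9 data call for a clarification and do not show a breach of intention to treat. The primary outcomes of acceptability, safety and feasibility are not affected.

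**What to change.** In Data management and statistical analysis, replace the repeated-measures ANOVA for each scale measured at both visits with ANCOVA of the week 9 value on baseline value, arm and site. A mixed model for both visits with a common baseline mean, a treatment effect at week 9, and site is equivalent. Name the adjusted week 9 difference between arms as the effect of interest and report it with a 95% CI.

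For the future sample size, report from the same model the residual SD and the baseline to week 9 correlation for each scale.

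Add a sentence on participants without a week 9 value that is consistent with the intention-to-treat label: who is in the analysis, which method is used, and on what assumption about the missing values. Do not present the new model as recovering the lost information.

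The cost is a change of wording. Baseline, arm and site are already collected, and no visit, measurement or participant is added.

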### Sample size

This proof-of-concept study will recruit 60 participants per group (ie, total sample size of 120). This will allow the researchers to gain preliminary data on the primary outcomes of safety, feasibility and acceptability of the HOLOBalance intervention. This will also provide sufficient data to explore trends for effectiveness and to allow for sample size estimates to be drawn up for a future trial.

### Study oversight

Trial steering committees and trial management groups will be formed to oversee the conduct of the research according to predetermined terms of reference.

### Patient participant involvement

As part of the larger HOLOBalance project, the research consortium has performed extensive patient participant involvement with older adults, discussing the study design, exergames and the supporting technologies with approximately 75 older adults in total.

## Ethics and dissemination

This study has received institutional ethical approvals in Germany (reference: 265/19) and Greece (reference: 9769/24-6-2019) and from the Health Research Authority in the UK (reference: 19/LO/1908). All amendments to the study protocol which may impact on the integrity of the study, or the data are required to receive approval by the research ethics committee prior to their implementation.

Findings from this study will be provided as lay reports to participants, disseminated to community groups via community partners and will be submitted for peer-reviewed publications. Additionally, electronic data will be anonymised and uploaded to a data repository (Zenodo) that supports restricted access. Electronic data will not be made publicly available and access will to the dataset will only be provided by the data management board of the HOLOBalance research consortium. Use and reuse of the pilot dataset will be subject to the licence under which the data objects were deposited.
